*Motivation for Physical Activity.* To assess motivation to practice physical-sports activity, an adaptation of the Behavioural Regulation in Exercise Questionnaire (BREQ-3; [48]), validated for the Spanish context by González-Cutre et al. [49], will be used. This scale begins with stem “I exercise because…”, followed by 23 items, grouped into six factors that measure intrinsic motivation (i.e., “it’s fun and satisfying to exercise”), integrated regulation (i.e., “it is consistent with my lifegoals”), identified regulation (i.e., “I think it’s important to make the effort to exercise regularly”), introjected regulation (i.e., “I feel a failure when I haven’t exercised in a while”), external regulation (i.e., “I feel under pressure from friends/family to exercise”), and amotivation (i.e., “I think exercise is a waste of time”). All the factors have four items except for the identified regulation, which has three. The response format is a Likert scale ranging from 1 (totally disagree) to 5 (totally agree).

*Intention to be Physically Active.* We used the Intention to be Physically Active (MIFA) questionnaire, created by Hein et al. [50] and adapted to the Spanish context by Moreno-Murcia et al. [51]. This instrument was developed with Spanish primary school students [52]. The scale is preceded by the phrase, “Regarding your intention to take up a sporting activity ...”, and comprises 5 items (i.e., “I am interested in developing my physical fitness”). The response format is a Likert scale ranging from 1 (totally disagree) to 5 (totally agree).

*Perception of Physical Activity Levels.* The Spanish-validated scale of Benítez-Porres et al. [53] was used to assess PA in children. This self-administered questionnaire measures moderate to vigorous PA performed in the last seven days in students. It consists of ten items, nine of which are used to calculate the activity level. The other item assesses whether any illness or other event prevented the child from doing their regular activities in the last week. The items are scored from 1 to 5.

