### 2.4. Statistical Analysis

The primary outcome will be changes in the levels of students’ motivation for out-of-school PA. Secondarily, perceived exercise autonomy support, the intention to be physically active, perception of PA levels, engagement in PE and academic performance will also be assessed. For this purpose, firstly, the nature of the variables will be taken into account through the application of normality, validity, and reliability tests. Secondly, the principles of independence, normality, linearity and variance of the study variables will be tested for general linear model analyses. Thirdly, intergroup and intragroup differences will be analysed with repeated-measures ANOVA or nonparametric tests such as McNemar’s or the Kruskall–Wallis tests, as appropriate. For continuous variables, Bonferroni-corrected multiple paired *t*-tests will be calculated to determine intra-group (i.e., between the experimental and control group) and inter-group (i.e., between the pre-test and post-test) differences. For categorical variables, a chi-square test will be performed. While Cramer’s V will be used to describe the degree of association between categorical variables and experimental and control schools, McNemar’s test will be used to analyse baseline and post-intervention differences in categorical variables in experimental and control schools, respectively. Effect sizes will be assessed using Partial Eta Squared (η_p_^2^) and Cramer’s V values for continuous and categorical variables, respectively. Effect sizes will be considered small, moderate or large when η_p_^2^ is greater than 0.01, 0.06 and 0.14, respectively, and when Cramer’s V is greater than 0.10, 0.30 and 0.50, respectively. Significance will be set at *p* < 0.05 for all analyses.

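### The non-parametric tests named as alternatives to repeated-measures ANOVA do not, as described, test the between-arm difference in change that the primary outcome needs

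*Protocol article*

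**What the plan says.** Section 2.4 of the protocol article defines the primary endpoint as a change: "The primary outcome will be changes in the levels of students’ motivation for out-of-school PA". Section 2.3 measures it with the BREQ-3, a stem "followed by 23 items, grouped into six factors that measure intrinsic motivation" and five further types of regulation, each item scored 1 to 5. Sections 2.1 and 2.2 give two arms of three schools each and three waves (February, June, October).

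Section 2.4 then sets out three steps:

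1. "the nature of the variables will be taken into account through the application of normality, validity, and reliability tests".
2. "the principles of independence, normality, linearity and variance of the study variables will be tested for general linear model analyses".
3. Differences between and within groups are then examined by repeated-measures ANOVA "or nonparametric tests such as McNemar’s or the Kruskall–Wallis tests, as appropriate".

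Later in the same section McNemar's test receives a narrower job: "McNemar’s test will be used to analyse baseline and post-intervention differences in categorical variables in experimental and control schools, respectively". The section does not say which score a Kruskal-Wallis test would be run on. It names no arm-by-time contrast and no rank method for a two-arm, three-wave design.

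**The concern.** An alternative to the main analysis should answer the same question under weaker assumptions. Here the question is whether motivation changes more in the experimental arm than in the control arm. The two tests offered as examples answer other questions. One asks whether a binary status shifts within a single arm. The other asks whether independent groups differ on one value per child.

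If preliminary tests lead the analyst from the ANOVA to one of these, the hypothesis changes along with the method. A standing difference between arms could then be reported as an effect, or a real effect could be hidden by one. With three schools per arm, drawn from a convenience sample of six, some baseline difference is plausible, although the article gives no figure for it. The decision would also be made after the data had been examined.

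**Working it through.** **Step 1: match each test to the outcomes.** The outcomes in section 2.3 are a 12-item support scale (1 to 7), BREQ-3 factor scores, intention, perceived activity level and engagement (all 1 to 5), and grades averaged over four subjects. None is defined as binary.

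- *McNemar* needs paired binary data, so every one of these outcomes would have to be dichotomised first. It works within one arm and does not compare arms.
- *Kruskal-Wallis* needs independent groups with one value per child. On June scores it compares the arms at June and ignores February. Over the four arm-by-time cells it treats two measurements on the same child as independent. On June minus February change scores, compared between two arms, it does test arm by time for that pair of waves.
- Neither gives a single test across all three waves.

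**Step 2: simulation inputs.** Section 2.4 gives no figure to reproduce on this point.

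- From the article: a minimum of 345 pupils in two arms, 345 / 2 = 172.5, taken as 172 per arm; significance at 0.05.
- Assumed: two-sided testing, SD 1, pre-post correlation 0.6, two waves, scores in steps of 0.25 limited to 1 to 5, shifts of 0.3, a cut at 4 for McNemar, no school clustering; 3,000 runs per setting.

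With two arms and two waves, the t-test on change is the repeated-measures ANOVA interaction test.

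**Step 3: share of runs with p < 0.05.**

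| Test | (a) Baseline gap 0.3, no effect | (b) Time trend 0.3 in both arms, no effect | (c) Baseline gap −0.3, true effect +0.3 |
|---|---|---|---|
| Kruskal-Wallis, June scores | 0.78 | 0.04 | 0.05 |
| Kruskal-Wallis, four arm-time cells | 0.83 | 0.97 | 0.81 |
| McNemar within experimental arm | 0.03 | 0.66 | 0.54 |
| Kruskal-Wallis, change scores | 0.05 | 0.04 | 0.85 |
| Arm-by-time test | 0.05 | 0.05 | 0.86 |

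In (a) and (b) a valid test of the trial's question should reject in about 5% of runs. In (c) it should detect the effect.

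**Step 4: closed-form check of the 0.78.** With two groups, Kruskal-Wallis is equivalent to the rank-sum test, whose efficiency relative to the t-test under normality is 3/π = 0.955. The expected test statistic is

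gap × √(n/2) × √0.955 = 0.3 × √86 × √0.955 = 0.3 × 9.274 × 0.977 = 2.72.

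The rejection probability is Φ(2.72 − 1.96) = Φ(0.76), about 0.78, which agrees with the simulation. The same formula gives about 15% for a gap of 0.1 SD and 44% for 0.2 SD. The pre-post correlation does not enter, because a June-only test does not use baseline.

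**The case against.** Several points on the other side are sound.

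- **Kruskal-Wallis can be used properly.** A reader might infer that it is incapable of testing arm by time. It is not: on change scores it holds its error rate (0.04 to 0.05) and has power of 0.85 against 0.86 for the interaction test. Since the primary outcome is defined as change, this may be what was intended. The article does not say so, and that use covers one pair of waves only.
- **McNemar may never have been meant for BREQ-3 scores.** The list opens with *such as*, and the later sentence ties McNemar to categorical variables, so the phrase may mean choosing by type of variable. No sentence applies it to motivation scores. Even so, it is named as an alternative to the ANOVA, and no listed outcome is categorical as defined.
- **No normality rule is written down.** It is tempting to say that the protocol switches tests on a failed normality test. That is an inference from the order of the steps. Nor does the article give score distributions from which to predict that the scores would fail.
- **The 78% measures neglect of baseline.** It is the power of a June-only comparison to detect a gap that was put in, and a t-test on June scores would do much the same.
- **Baseline and school adjustment.** The stated ANOVA is not described as including school or a baseline covariate either, so their absence does not distinguish the fallback from the main analysis.
- **Detail may sit in an analysis plan.** The exact rank procedure could. But the article names specific tests for this role, and as described they do not fill it, so this is more than an omission.

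**Conclusion.** The point holds in limited form. As described, McNemar and raw-score Kruskal-Wallis do not replace the arm-by-time comparison, and section 2.4 does not commit to one primary analysis. A move from the ANOVA to either test could change the question as well as the method.

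The size depends on inputs that the article does not give. With a stable gap of 0.3 SD, 172 pupils per arm and no clustering, the false-positive share is about 78% for Kruskal-Wallis on June scores and about 5% for either test of change. With smaller gaps it falls to about 44% (0.2 SD) and 15% (0.1 SD). With no gap it is the nominal 5%. These figures illustrate one possible use of the fallback. They are not the trial's expected error rate, because the article neither specifies a June-only test nor says that the fallback will be used.

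**What to change.** In section 2.4, for all scale scores and grades:

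1. Remove McNemar and raw-score Kruskal-Wallis as alternatives to the repeated-measures ANOVA.
2. Fix in advance one primary analysis of the between-arm difference in change, to be used whatever the normality tests show. It can be the arm-by-time contrast or the follow-up score adjusted for baseline. State which wave or waves it uses.
3. If residuals are clearly skewed, add a rank-based sensitivity analysis of the same contrast, for example on change scores or rank-transformed scores.
4. Keep McNemar and chi-square for variables that are genuinely categorical.

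How school enters the model is a separate question that affects the stated ANOVA equally, and this change does not settle it.

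Cost: a few sentences of analysis wording and one sensitivity analysis. Design, data collection and sample size are unaffected.

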## 2. Methods

### 2.1. Design and Participants

This quasi-experimental study will be carried out in Cáceres (Extremadura, Spain). Convenience sampling will be conducted in six different Primary Schools. Three schools will be randomly assigned to the control school and the other three schools to the experimental school. The sample size will be estimated using the following formula: *n* = (Z)^2^ (*p*(1 − *p*) e^2^), where “*n*” is the sample size, Z = 1.96 (95% confidence interval), *p* = number of 4th and 5th primary school students in the city where the study will be conducted (±3350 students), and e = margin of error (3%). The minimum sample size (considering a 10% non-response) will be 345 students. All the schools will have similar socio-demographic and built-environment characteristics [37]. School courses in Extremadura run from early September to mid-June, with a Christmas break from late December to early January and a break around March or April for the Easter holidays. As seen in Figure 1, assessments will be completed at baseline at the beginning of the school course (Term 1, February) and after the intervention (Term 2, June). A follow-up measurement will be conducted at the beginning of the following school course (Term 3, October). The study has been agreed upon by the Ethics Committee of the University of Extremadura (120/2018) and follows the guidelines of the Declaration of Helsinki.

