### 2.2. Intervention Based on SDT in Primary School

In February, an informative document will also be given to the families or legal guardians, accompanied by the informed consent to be signed. The research team will go to the schools to collect the data on certain days according to the organisational availability of the teachers during lessons. There will always be at least one research team member in the classroom while the students complete the questionnaires to solve any possible doubts. The questionnaires will be completed on paper in approximately 40 min. The variables described in Section 2.3 will be measured three times: (i) before the intervention (February); (ii) after the intervention (June); and (iii) a follow-up measure at the beginning of the following school year under the same conditions as in the two previous measures (October).

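### Section 2.4 swaps the intra-group and inter-group labels and assigns paired t-tests to the experimental-versus-control comparison, where no pairs exist; the error is confined to the t-test step

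*Protocol article*

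**What the plan says.** Section 2.4 sets the target: "The primary outcome will be changes in the levels of students’ motivation for out-of-school PA". Under Section 2.3 this is measured with BREQ-3 Likert factors, so it is analysed as a continuous variable. Under Section 2.2 the outcomes are taken in February, June and October.

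Two consecutive sentences of Section 2.4 then deal with group and time differences. The first is general: "Thirdly, intergroup and intragroup differences will be analysed with repeated-measures ANOVA or nonparametric tests". The second concerns continuous variables only. It names paired t-tests with Bonferroni correction, and says that they serve "to determine intra-group (i.e., between the experimental and control group) and inter-group (i.e., between the pre-test and post-test) differences". No other t-test is named in the article.

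On how the arms are formed, Section 2.1 says: "Three schools will be randomly assigned to the control school and the other three schools to the experimental school". No matching of pupils or schools across arms is described.

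**The concern.** The second sentence contains two separate errors. The labels are the wrong way round: experimental versus control is the between-group comparison, and pre-test versus post-test is the within-group one. In addition, a paired test is prescribed for both. It suits repeated measurements on the same pupil. It does not suit a comparison of two sets of different pupils.

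The primary outcome falls in this branch. An analyst who follows the sentence literally cannot run the between-arm test. An analyst who runs the part that works obtains one pre-post p-value in each arm. Those p-values answer whether scores moved in that arm between February and June. Maturation, the school calendar or repeated exposure to the questionnaire could move scores in both arms. Setting one p-value beside the other does not estimate the difference in change between arms.

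**Working it through.** **Step 1. Does relabelling repair the sentence?** With the labels exchanged, it would read: paired t-tests for within-arm differences (pre versus post) and for between-arm differences (experimental versus control). The first half becomes correct. The second half is still wrong, because three whole schools go to each arm and a pupil in one arm has no partner in the other. So this is more than a label slip.

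**Step 2. How does the same section treat categorical variables?** It uses McNemar's test for baseline versus post within each arm, and chi-square with Cramer's V for association with arm. There, the paired test is for time and the independent-groups test is for arm. The continuous branch lacks the second of these at the t-test step.

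**Step 3. Does anything else in the section cover the arm comparison?** Yes. The preceding sentence assigns intergroup differences to repeated-measures ANOVA, and the effect size for continuous variables is partial eta squared, which belongs to an ANOVA and not to paired t-tests. With arm as a factor, its arm-by-time term estimates the difference in change.

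**Step 4. Illustration of what within-arm p-values would do if read as the arm comparison.** There is no figure in the article to reproduce. Inputs:
- 345 pupils (Section 2.1). An equal split is assumed: 345/2 = 172.5, taken as n = 172 per arm.
- Significance level 0.05 (Section 2.4); two-sided is assumed.
- Further assumptions: SD of the change score = 1, independent pupils, no Bonferroni correction, no intervention effect, and the same true change d in both arms.

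Each within-arm test is centred at d√n, with √172 = 13.11. Its rejection probability is approximately π = Φ(d√n − 1.96), plus a second tail that matters only near d = 0. With the arms independent, experimental significant and control not has probability π(1 − π). A simulation of 10,000 trials per row agrees:

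| d (SD) | d√n | π | π(1 − π) | simulated: experimental significant | simulated: experimental only | simulated: between-arm test of change |
|---|---|---|---|---|---|---|
| 0 | 0 | 5.0% | 4.8% | 5.2% | 4.9% | 5.3% |
| 0.10 | 1.31 | 25.8% | 19.2% | 25.9% | 19.7% | 5.1% |
| 0.15 | 1.97 | 50.3% | 25.0% | 50.1% | 24.6% | 4.9% |
| 0.20 | 2.62 | 74.6% | 18.9% | 74.1% | 19.6% | 4.9% |
| 0.30 | 3.93 | 97.6% | 2.4% | 97.4% | 2.2% | 4.8% |

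π(1 − π) cannot exceed 25%, so the 0.15 SD row is essentially the worst case.

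**Step 5. Two limits of the illustration.**
- *Bonferroni.* Correction moves the peak but does not remove it. If, for example, three time contrasts were corrected for within each arm (an assumption), the critical value is 2.39 at 0.05/3. The 25% peak then sits at d = 2.39/13.11 = 0.18 SD.
- *Clustering.* The 5% in the last column holds only for independent pupils. With 345/6 = 57.5 pupils per school and an assumed intraclass correlation for change of 0.01–0.02, the design effect is 1 + 56.5 × 0.01 = 1.57 to 1 + 56.5 × 0.02 = 2.13. A pupil-level test that ignores school would then reject a true null with probability 2[1 − Φ(1.96/√1.57)] ≈ 12% to 2[1 − Φ(1.96/√2.13)] ≈ 18%. The between-arm contrast therefore has to account for school.

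**The case against.** A reader might infer that the plan has no valid way to estimate the intervention effect. The text does not support that. A between-arm analysis is planned one sentence earlier, with a matching effect size, and it is available for the primary outcome. This part of the objection stands, and it confines the error to the t-test step.

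A reader might also infer that the trial will declare success when the experimental arm is significant and the control arm is not, at a false-positive rate of up to 25%. The article states no such rule. The figures in the working describe a possible misreading. They peak near one particular common change, and they leave out the Bonferroni correction that the article does specify. This also stands, so the figures serve only as illustration.

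It can further be said that the article does not name the arm-by-time term or use the February score as a covariate. Neither is an error. Which ANOVA term is primary is commonly left to a fuller plan that is not shown here. The February score also enters a repeated-measures ANOVA as a time point; covariate adjustment would add precision but would not correct a mistake.

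Finally, the swap may be a drafting slip, as the sound treatment of categorical variables suggests. That is plausible for the labels. It does not explain away the paired test, which stays assigned to the arm comparison after the labels are exchanged. Nor is this a detail left to an analysis plan: the article states the method, so a later plan must either contradict the sentence or inherit it.

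**Conclusion.** The point holds for the t-test sentence: its labels are reversed, and its paired test cannot make the between-arm comparison assigned to it. This follows from the article's own wording and from allocation by school, with no numerical assumption. The planned repeated-measures ANOVA limits the damage. It should be fixed before analysis, but it does not invalidate the plan.

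The size of the risk is conditional. If within-arm p-values were used in place of the arm comparison, the misleading pattern would occur in about 2% to 25% of null trials over common changes of 0 to 0.30 SD, under the assumptions listed in the working.

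**What to change.** - Correct the labels: intra-group for pre versus post within an arm, inter-group for experimental versus control.
- Restrict paired t-tests to descriptive within-arm time contrasts.
- State that the conclusion on the primary outcome rests on the between-arm contrast. This can be the arm-by-time term or, preferably, the difference in June score adjusted for the February score, with a 95% confidence interval. The October score, adjusted in the same way, would be secondary.
- Fit school as a random effect, with small-sample degrees of freedom (six schools less two arms leaves about 4). School should not be a fixed effect, because each school lies wholly within one arm and fixed school terms would be aliased with arm.

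The cost is a few sentences of analysis text. All the scores needed are already to be collected at the three planned visits.

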## 3. Discussion

PE can be considered a potential tool to develop interventions aimed at promoting PA in students, in line with the curricular objectives addressed in this subject [58]. However, the number of studies examining interventions to promote school PA is relatively small, and more interventions should be reviewed and analysed in more detail. The goal of the study of this protocol is for the PE teacher to apply a series of SDT-based motivational strategies for PA that support autonomy, competence, and relatedness in primary education students to improve their motivation for in-class PA and, consequently, for extracurricular PA. The intervention will be grounded in the SDT [13] and is expected to make a unique contribution to knowledge in four areas: (i) it will outline the development and implementation of a replicable teacher-training programme based on SDT, where strategies and techniques to support of three BPN are jointly designed and implemented in the teachers’ PE classes and which promote free-time PA; (ii) it will test the rarely proven effectiveness of SDT-based strategies delivered by PE teachers to promote Primary Education students’ participation in PA in their free time; (iii) through the different strategies, work among peers and the participation of families in physical-sports activities in their leisure time will be encouraged, thus trying to involve significant agents in the students’ learning process; and (iv) it will evaluate the long-term effectiveness of the intervention to promote PA behaviour through the four- and six-month post-intervention follow-up of behavioural and theory-based outcomes.

Despite the proven importance of PE for the development and learning of students in the practice of PA in their leisure time, so far, interventions to promote this through PE are scarce [8]. For example, a previous study [36] demonstrated the effectiveness of a PE-delivered intervention aimed at promoting PA participation in primary schools. However, the intervention program of that study included two weekly hours of PE, with a methodology of support for autonomy. In other words, strategies were used during PE classes to encourage students’ PA in their free time. In this sense, the present study will try to elaborate and put into practice strategies adapted to PE classes to promote out-of-school PA without modifying the programme initially established by the teachers. The study by Moreno-Murcia and Sánchez-Latorre [36] trains teachers to learn autonomy support techniques taught by another teacher. However, research has shown that student motivation can be strengthened if teachers support the three BPNs (i.e., autonomy, competence, and relatedness). On the other hand, motivation can be weakened and lead to maladaptive outcomes if teachers use thwarting techniques [59]. In our case, we propose a more complete training, addressing autonomy, competence and relatedness, and taught by a research team of university teachers whose line of research is linked to the SDT theoretical framework.

Beyond examining the expected outcomes of the intervention based on previous research, that is, increasing students’ motivation for PA and their leisure-time PA levels, this project’s findings can be used more holistically. For example, the programme is expected to generate students’ future habits of autonomous PA, improve their perception of competence in different PA, and motivate families to practice PA. Thus, considering the importance of promoting in- and out-of-school PA, we recommend developing SDT-based strategies in PE classes to promote an active life. In this sense, it is also worth highlighting the methodological benefits that this intervention will have in the school context. Firstly, with respect to the PE teachers who will receive a training programme in motivational theories (i.e., SDT), which will allow them to change or reinforce their approach to teaching classes in order to make their students more autonomous, competent and to improve social bonds both inside and outside of the school context. Furthermore, this training programme will also be important to encourage autonomous learning on the part of teachers so that they are in a continuum of renewal that allows them to adapt their classes to new social demands. Secondly, all the didactic materials and resources in the intervention programme will remain in the school for future years. This means that not only students in 4th- and 5th-grade of primary education will benefit from these strategies, but that students in other academic grades will have the possibility of taking advantage of these resources to improve their motivation towards PA in their leisure time, their engagement, their intention to be physically active and thus establish the bases so that this age group can increase their levels of PA.

